## Abstract

**Background:**

Individuals with disabilities living with chronic health conditions require self-management programs that are accessible, sustainable, inclusive, and adaptable. Health coaching is an effective approach to promoting behavior change in self-management. Health coaching combined with telehealth technology has the potential to improve the overall quality of, and access to, health services.

**Objective:**

This protocol outlines the study design for implementing the My Health, My Life, My Way intervention. The study will assess the feasibility, acceptability, and preliminary efficacy of the intervention for people with disabilities and optimize it.

**Methods:**

The My Health, My Life, My Way study is a 4-arm randomized controlled trial evaluating the delivery of a 6-month intervention involving telecoaching, inclusive educational content, and technology access for 200 individuals with chronic conditions and physical disabilities. This study uses the engineering-inspired multiphase optimization strategy (MOST) framework to evaluate intervention components and assess whether a combination or lack of individual elements influences behavior. Participants will be randomized to 1 of 4 study arms: scheduled coaching calls and gamified rewards, no scheduled coaching calls and gamified rewards, scheduled coaching calls and flat rewards, and no scheduled coaching calls and flat rewards.

**Results:**

The My Health, My Life, My Way study was approved by the institutional review board of the University of Alabama at Birmingham, and recruitment and enrollment will begin in May 2023. Data analysis is expected to be completed within 6 months of ending data collection. This clinical trial protocol was developed based on the SPIRIT (Standard Protocol Items: Recommendations for Interventional Trials) 2013 statement.

**Conclusions:**

The My Health, My Life, My Way study will help to optimize and improve our understanding of the feasibility and efficacy of a web-based self-management program for people with physical disabilities and chronic conditions. More specifically, My Health, My Life, My Way will determine which combination of interventions (coaching calls and gamification) will result in increased participation in self-management programming. The My Health, My Life, My Way intervention has the potential to become a scalable and novel method to successfully manage chronic conditions in people with disabilities.

**Trial Registration:**

ClinicalTrials.gov NCT05481593; https://clinicaltrials.gov/ct2/show/NCT05481593

**International Registered Report Identifier (IRRID):**

PRR1-10.2196/31694

## Introduction

### Background

The Centers for Disease Control and Prevention (CDC) defines chronic diseases as conditions that last ≥1 year and require ongoing medical attention or limit activities of daily living or both. In the United States, 6 in 10 adults are reported to have at least 1 chronic condition, whereas 4 in 10 adults are reported to have ≥2 chronic conditions [1]. The prevalence statistics of these individual conditions, which include diabetes, heart disease, and stroke, present an even more disturbing picture; for example, diabetes affects 12.2% of the overall American adult population and 25.25% of the population aged >65 years [1,2]. Similarly, approximately 1 in 3 deaths in the United States are attributed to heart disease, stroke, and other cardiovascular diseases [3]. In 2020, the CDC identified chronic diseases as the leading causes of death and disability as well as the leading drivers of annual health care costs of US $3.5 trillion [1].

Although physical disabilities increase the risk of developing chronic conditions, the inverse also occurs [4,5]. In fact, chronic conditions are the leading causes of disability [1]; for example, a report on the top causes of disability among adults in the United States found arthritis, heart conditions, and diabetes among the top 6 causes of disability [6]. This bidirectional relationship between disabilities and chronic conditions is indeed well documented. Diabetes is associated with a substantial increase in the risk of mobility disability [4]. Among older participants with diabetes (aged ≥60 years), diabetes was correlated with a 2- to 3-fold increased odds of not being able to perform each task of walking one-fourth of a mile, climbing stairs, or doing housework among both men and women [2]. In brief, chronic conditions and disability exist in a tightly knit closed loop, with the onset of any of these factors exposing the individual to increased risk for the other.

Current science has enabled multiple approaches to managing chronic disease conditions [7,8]. Approximately two-thirds of chronic disease management is conducted in primary care settings globally, whereas approximately one-fifth is conducted in community-based settings [9]. An extensive review of 145 chronic disease management studies notes that self-management support is the most frequently used intervention approach and the most effective strategy [7]. A meta-analysis specifically focused on chronic disease self-management strategies for diabetes, hypertension, and osteoarthritis spanning 53 randomized controlled trials concludes that these programs are indeed effective for people with diabetes or hypertension [10].

Within these programs, multiple approaches have been used to implement self-management programs. Health coaching is one of the most common and cost-effective mechanisms of delivering self-management programming [11-13]. Health coaches are health care professionals who are trained in relevant areas of focus based on the disease or condition being managed. Positive aspects of health coaching include removal of barriers and increased retention with human interactions that support individualized interventions. Health coaching can be conducted either synchronously or asynchronously, which further allows individualization to meet participant needs. However, health coaching has 2 challenges—resources and availability of time spent with participants—both of which affect the scalability of health coaching [14]. In addition to health coaching, gaming features incorporated into telehealth interventions have the capability to promote adherence and compliance and warrant adoption in disability-related self-management programs. Such features include obtaining points, participating in challenges or competitions, social communication, and person-centered customizations such as avatars. There is broad appeal to incorporating gaming elements into self-management programs for individuals with physical disabilities [15].

Although self-management programs are effective for behavior change in managing health conditions, individuals with physical disabilities who also experience chronic conditions lack inclusive and accessible self-management programming to positively affect their own behavior change. People with disabilities experience barriers that are different from those experienced by people without physical disabilities, including nutritional and dietary concerns, as well as barriers to physical activity (PA) participation. More specifically, these barriers include lack of accessible environments, appropriate equipment (eg, wheelchair accessibility), and low health literacy and knowledge [16-19]. As there are few studies evaluating the impact of self-management programs on individuals with physical disabilities, there is a demand to provide and optimize holistic self-management programming to those with physical disabilities who also experience chronic conditions.

In the goal to improve chronic disease management for people with disabilities, we propose the development of an inclusive telecoaching self-management program. To make the telecoaching approach sustainable and scalable, artificial intelligence techniques are used to reduce the time that health coaches spend communicating with each participant.

### Objectives

This study is structured to serve as the optimization phase of the multiphase optimization strategy (MOST) framework and involves efficient randomized experimentation to estimate the effectiveness of individual intervention components and identify the optimal intervention package to improve the primary outcome, health-related quality of life after 6 months [20,21]. We will specifically focus on the physical functioning and emotional well-being subscale scores. The feasibility and acceptability of the My Health, My Life, My Way intervention will also be studied. This study protocol has been developed by using the SPIRIT (Standard Protocol Items: Recommendations for Interventional Trials) 2013 statement [22]. It has been registered at ClinicalTrials.gov (NCT05481593).

## Methods

### Study Overview

#### Coaching Calls

Telehealth programs provide several advantages for individuals who want to improve their overall health and promote positive behavior change [23]. A substantial advantage of such programs is scalability or widespread availability, which allows participants to engage domestically or internationally. Many of these programs use human-to-human interactions to deliver web-based content to their clients or patients. In addition, some programs now implement artificial intelligence in conjunction with human interactions; for example, certain health care industries use chatbots to provide satisfactory and engaging interactions. A chatbot is a software platform that mimics human interaction with individuals using text or voice capabilities across different technologies, such as computers and smartphones. Within the literature, there is an acceptable level of satisfaction with using chatbot technology [24,25]. Because of the perceived benefits of telehealth programs using human interactions as well as web-based chatbots, it is necessary to evaluate whether scheduling coaching calls are necessary for successful self-management of chronic conditions. Each study arm in this project will incorporate either scheduled coaching calls or no scheduled coaching calls. Those receiving scheduled coaching calls will receive weekly calls with trained health coaches. Although individuals not receiving coaching calls will not have regular contact with a health coach, these participants can still contact health coaches using texting, chatting, or calling to initiate on-demand communication with the health coaching team.

#### Gamification

Gaming technologies have displayed a high level of adherence and engagement characteristics, and this has led to the gamification of telehealth interventions. Gamification refers to the use of game design elements in nongame contexts and is being used across a variety of telehealth interventions to promote treatment adherence [15]. Within telehealth intervention, gamification elements provide immediate feedback, continuous progress reporting, points, badges, levels, challenges, competitive components, and avatar and profile functionality [15]. There is a broad appeal to including gamification elements in telehealth studies for multiple reasons, such as (1) supporting transition to increased levels of intrinsic motivation, (2) deliverability through multiple technology streams, (3) appeal across different audiences, and (4) appeal in health and fitness industries [15]. However, the impact of gamification features on redeemable rewards is unclear [26]. More specifically, it is unknown how individuals’ intrinsic motivation will be affected by redeemable rewards. Within this study, participants will receive either gamified rewards or flat rewards. For those receiving gamified rewards, there will be an increase in the number of redeemable points the longer adherence and participation are maintained. Those receiving flat rewards will receive a fixed number of points for regular participation in the intervention. Elements of participation include but are not limited to logging in to the platform, interacting with the educational content, and watching multimedia content. These variations in rewards will inform whether gamification features alone promote a shift from extrinsic to more intrinsic motivation and whether this is associated with increased adherence and engagement or whether financial incentives are necessary to promote study adherence.

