#### MOST Framework

Telehealth intervention studies typically use randomized controlled trial designs. However, telehealth interventions are comprehensive packages that include components such as coaching calls, educational content, texting, email, and mobile apps. Randomized controlled trials fail to reveal which components are responsible for any behavior change elicited during the intervention; rather, they only show whether the intervention package as a whole had any effect. Therefore, it is necessary to know which elements of telehealth interventions are needed or should be removed for a more efficient telehealth intervention. To optimize the My Health, My Life, My Way program, the MOST framework will be used to assess which study elements (coaching calls and gamification) elicit behavior change. The MOST framework, derived from engineering principles, is an efficient method to gather information on each intervention component or package and investigate whether the presence or absence of a component has an impact on the performance of other components [20,21,27]. Within this study, we will assess coaching calls (scheduled or on demand) and gamification (scaled rewards or flat rewards).

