### Participant Study Activities

#### Gamification Component

All participants, regardless of gamification variation, will be able to obtain points and badges on the platform. Participants can check their points status at any time during the study by logging in to the platform to view an itemized list for all badges and points. In addition, participants will be provided email notifications for all gamification updates. All activities, such as viewing and reading educational content and logging in to the platform, will automatically be updated on the platform. Health coaches will encourage participants to engage on the platform regularly. Those not receiving scheduled coaching calls who exercise the on-demand coaching option will be encouraged by a health coach to use the platform regularly.

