## Discussion

### Many Important Implications

The aim of this paper was to detail the study protocol used to develop a web-based self-management program for individuals with physical disabilities who also experience chronic conditions by using artificial intelligence techniques. The incorporation of variations in coaching calls and gamification will be evaluated to determine which combination of intervention components is the most effective for personal self-management. As the My Health, My Life, My Way program will be implementing a 4-arm protocol using the MOST design, many important implications can be drawn based on the findings of this study. The findings will assess what resources are required by self-management programs to maintain high levels of adherence and engagement. For coaching calls, if scheduled coaching calls are not as effective at promoting self-management as on-demand coaching calls, this would result in a reduced demand for excess resources, including the number of health coaches, monetary expenses, training, and daily availability of health coaches. If scheduled coaching calls are shown to be more effective than on-demand coaching calls, future web-based self-management programs should consider bolstering the resources to provide appropriate health coaching with qualified health coaches. Within the gamification context, the results from this study will inform future programming for individuals with physical disabilities who also experience chronic conditions. If gamified rewards are shown to be more effective than the fixed rewards model, self-management programs should consider using appropriate methods to promote extrinsic motivation by providing desirable incentives for behavior change. If fixed rewards are shown to be more effective than gamified rewards, this could indicate that a participant’s intrinsic motivation to improve their self-management is more important than extrinsic rewards such as redeeming increasing monetary incentives to promote behavior change.

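### The scaled-versus-flat reward contrast cannot show whether gamification alone shifts motivation or whether financial incentives are needed

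*Protocol article*

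**What the plan says.** The Gamification section of the protocol article defines the two levels of the reward factor. At the gamified level, "there will be an increase in the number of redeemable points the longer adherence and participation are maintained". At the other level, "Those receiving flat rewards will receive a fixed number of points for regular participation in the intervention". The MOST Framework section gives the same contrast in brief: "we will assess coaching calls (scheduled or on demand) and gamification (scaled rewards or flat rewards").

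The Gamification section also states what the factor is meant to show: "These variations in rewards will inform whether gamification features alone promote a shift from extrinsic to more intrinsic motivation", and whether that goes with better adherence and engagement, or else "whether financial incentives are necessary to promote study adherence".

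The Gamification Component section describes what is delivered: "All participants, regardless of gamification variation, will be able to obtain points and badges on the platform". It adds that "participants will be provided email notifications for all gamification updates", without limiting this to particular arms. The Intervention Design section and Table 1 nevertheless label two of the four arms as having rewards that do not depend on gamification.

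The Discussion (Many Important Implications) says that an advantage of fixed over gamified rewards could mean that a participant's "intrinsic motivation to improve their self-management is more important than extrinsic rewards", with increasing monetary incentives given as the example of such rewards.

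**The concern.** A randomised factor answers only the question set by the difference between its levels. To learn what gamification does alone, some participants must go without it. To learn whether financial incentives are necessary, some must go without those. To learn whether motivation shifts from extrinsic to intrinsic, motivation must be measured. The reward factor varies how points accrue and, as described, does none of these three things.

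What is at stake is what the trial may conclude. This is the optimisation phase of the programme, and the Discussion tells future self-management programmes how to act on the result for the reward factor. If the report follows the article as written, a difference between two reward schedules would be presented as evidence on gamification as such, on the need for payment and on the type of motivation at work.

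**Working it through.** **The plan's own figure.** The Sample Size section gives 200 enrolled, 20% attrition, 160 completers, two-sided 5% type I error, 80% power, a baseline–outcome correlation of 0.6 and a detectable main effect of d = 0.36. With 1:1:1:1 allocation, each level of a factor has 80 completers.

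- Residual SD after adjustment for baseline: √(1 − 0.6²) = 0.8.
- Detectable difference: (1.960 + 0.842) × 0.8 × √(2/80) = 0.354 by the normal approximation, and 0.357 with the t distribution on 155 df.
- Power at d = 0.36: 0.812 (normal) or 0.807 (t).
- Completers needed for d = 0.36: 78 per level, 156 in all; 156/0.8 = 195 enrolled.

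The stated figure reproduces. It is the power to detect a difference between the two reward schedules in quality of life, and nothing in this point disturbs it.

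**Is there a comparator for gamification alone?** The Gamification section counts points and badges among the elements of gamification. The Gamification Component section gives both to everyone. So 0 of 4 arms lack these elements, and the label for the two flat-reward arms in Table 1 does not match what those arms receive. The only difference the article describes between the levels is how points accrue.

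**Is there a comparator for financial incentives?** Both levels are called rewards. The article writes that points are redeemable only for the gamified level, so two cases need to be considered.

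- *Flat points are redeemable.* This is the natural reading: the section introduces the factor through redeemable rewards, calls the second level flat rewards, and the Discussion speaks of a fixed rewards model. Then no level lacks a financial incentive, and the contrast shows whether the schedule matters, not whether incentives are needed.
- *Flat points are not redeemable.* The levels would then differ in redeemability and in escalation together. The contrast could speak in part to financial incentives, but could not separate them from escalation. Points and badges would still be common to all arms.

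**Is motivation measured?** Table 2 and the outcome sections list quality of life, physical activity, self-efficacy, sleep, illness impact, depression, diet, medication adherence and beliefs about medication, and usability; current medications are also recorded. None is described as measuring intrinsic or extrinsic motivation. Feasibility Measures covers adherence and retention, and Auditing covers event logs and time on the platform; these record behaviour. The exit interviews take up to 30 participants after the study and ask about their experience with the platform, so they cannot show a shift in motivation by randomised arm.

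**Do the two interpretive passages agree?** The Gamification section asks whether gamification moves people towards intrinsic motivation. The Discussion would take an advantage of gamified rewards as a reason to promote extrinsic motivation, and an advantage of fixed rewards as a possible sign of intrinsic motivation. A fixed number of points given for participation is also an external reward, so neither direction of result separates the two kinds of motivation.

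**The case against.** The strongest reply is that these sentences are rationale and discussion, not objectives. The Objectives section sets out component effects on health-related quality of life, with feasibility and acceptability; Statistical Methods contains no hypothesis on motivation; and the MOST Framework section states the contrast correctly. The Discussion sentence is hedged and refers to increasing incentives. All of this stands, and it limits the point to interpretation. It does not remove it: the Gamification section is part of Methods and says without a hedge that the reward variation will inform these questions.

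Three stronger readings are tempting, and the article does not support them.

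- *Every arm receives redeemable points.* This is likely but is not stated for the flat level. The claim about necessity of incentives rests partly on this inference; the claims about gamification alone and about motivation do not.
- *A gamified advantage would simply reflect a larger payment.* Point values are not in the article, which may leave them to the full protocol, so a difference in total reward can be neither shown nor sized. Reward that grows with participation is also the component as defined, and testing it as it would be delivered suits an optimisation trial. Equalising the maximum value across levels would change the intervention and would equalise payment only for those who adhere fully.
- *The reward factor or its power is invalid.* It is not; the contrast and its stated detectable difference hold.

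**Conclusion.** The point holds as a mismatch between the design and some of the conclusions announced for it. With 0 of 4 arms free of points and badges, and no listed measure of motivation, the factor cannot show what gamification alone does or whether motivation shifts, at any sample size. It also cannot show that financial incentives are necessary if flat points are redeemable, as the wording suggests; if they are not, it could do so only in part, mixed with escalation. The tentative Discussion reading of a flat-reward advantage is unsupported because flat rewards are extrinsic too.

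The randomised comparison, its primary analysis and its power are unaffected. The factor validly estimates the effect of escalating versus flat rewards on quality of life and on adherence and engagement. No numerical correction follows. What changes is what the trial may claim.

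**What to change.** 1. In the Gamification section and in Many Important Implications, replace the conclusions on gamification alone, on intrinsic versus extrinsic motivation and on the necessity of financial incentives with one statement: the factor estimates the effect of escalating versus flat rewards on quality of life and on adherence and engagement.
2. In Intervention Design and Table 1, describe the two comparison arms as flat rewards, not as independent of gamification, and state whether flat points can be redeemed.
3. Report points earned and points redeemed by arm, so that any difference in total reward is visible when the factor is interpreted.

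These are text edits and one descriptive table. They need no change to the arms, the points schedule, the sample size or the primary analysis. The cost is a narrower claim about gamification. Keeping the wider claims would instead require a measure of motivation and an arm without the component in question.
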